#### Specific objective 3: Evaluate the effectiveness of the intervention in primary health care

This part of the interventions is composed by a quantitative and a qualitative component.

1. a Quantitative Component:

All PHC providers at the selected CESFAMs who have direct contact with users will be recruited for the study and will be expected to participate at all data collection time-points. A total sample size of at least 36 PHC providers per CESFAM with a total of 288 per arm its estimate (or 576 per data collection). Sample size for the proposed study was calculated in two steps. First, it was calculated with individual randomization. This calculation was based on the mean ± SD score for the OMS-HC scale was 48 ± 8.3 points, estimated with a sample of 798 PHC providers surveyed in FONDECYT N° 1160099 (34). This should be the average obtained in control CESFAM for the present study. Based on prior interventions in Canada (63), an estimated effect size of 10% in the intervention arm and a placebo effect of 3% in the control arm (from survey application) is expected. Thus, the average OMS-HC score in the intervention arm is expected to decrease to 43.2 ± 8.3 in the intervention group and 46.6 ± 8.3 in the control group (representing a decrease of 4.8 and 1.4 points, respectively). The standard deviation was assumed to remain the same in the intervention and calculations. To detect a statistically significant difference between intervention and control CESFAM, with an α = 5% and statistical power of 80%, the minimum sample size per arm is 94 individuals. Considering a 10% loss to follow-up in the intervention arm, 105 individuals per arm should be recruited with an individual randomization design. The minimum sample size was also calculated considering cluster randomized controlled design. Two elements were considered: (1) a minimum sample size of 105 and (2) an estimation of the intracluster correlation coefficient (ICC) for the study outcome (OMS-HC scale) (83). In this case, it was assumed the ICC to be ρ = 0.05, which is consistent with highest value reported in the literature for outcomes in primary care settings (74) and slightly higher than that reported in a study of a depression program in CESFAMs in Chile (84). Given the required sample size calculated based on individual randomization and the value of ICC = 0.05, the minimum number of clusters required is equal to: [105*0.05] = 5 clusters (75). However, a larger number of clusters would allow recruitment of a smaller number of individuals per cluster, maintaining an α = 5% and statistical power of 80% to detect differences between the control and intervention groups (85). For example, if 8 clusters per arm is considered (16 CESFAM total), it is necessary to recruit a minimum of 36 professionals per CESFAM. Thus, a minimum of the total sample of PHC providers to recruit would be 288 per arm (576 total). The validated, Chilean version of the Opening Minds Scale for Health Care Providers Scale (OMS-HC) (86), will be used as the primary outcome measure for PHC Professionals in the study. It will be applied at baseline, mid-point, end-point, with an expected 9-month interval between applications, and at 6-month follow-up.

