A minimum sample size of 27 PHC users per CESFAM was calculated (or 216 users per study arm, or 432 users total per data collection). For this sample size calculation, the mean ± SD for the ISMI score was 10.34 ± 4.74 points, estimated based on the results of FONDECYT N° 1160099 (34). A placebo effect of 1% was considered in the control group, and a 15% expected effect size was considered in the intervention group, based on the protocol for a similar intervention study completed in Canada (which estimated a higher effect of 19.5%; a more conservative estimate was selected for this calculation) (64). Thus, the mean of the scale would decrease to 10.23 ± 4.74 in the control group and to 8.79 ± 4.74 in the intervention group (an average decrease of 0.1 and 1.55 points, respectively). No change in the standard deviation was assumed, to be conservative with the calculation. To detect a statistically significant difference of this size between intervention and control groups, with a significance level of α = 5% and statistical power of 80%, 169 individuals are required in each group (intervention and control). Loss to follow-up it is not considered, as individuals recruited at the baseline and end-point data collection will not necessarily be the same, and this will be a cross-sectional sample. In the cluster RCT design, it is expected that the ICC of the ISMI score would be relatively low, as the CESFAM user population is more likely to be heterogeneous than the PHC providers. Assuming an ICC = 0.01, and considering the k = 8 clusters in each arm of the study (from PHC provider calculations), or 16 CESFAM total, it is necessary to recruit a minimum of 27 PHC users per CESFAM, or 216 users in each arm, for a total sample size of 432.

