### Data analysis

The data analysis will be conducted through months 42–48. Post data collection activities consider the following: (1) Data cleaning and evaluation, (2) Creation of derived variables, (3) Response rate calculation and (4) Bias evaluation.

It will be carried out using SAS 9.4 (specifically, using POC MIXED and PROC GENMOD) and R 3.5. Mixed-effect modeling will used for both PHC provider and user data, which will include individuals and CESFAMs as random effects and group (intervention/control) as fixed effects. The technique is appropriate to analyze cluster randomized controlled trials because these models can account for the possible dependence between responses of users and PHC providers within the same CESFAM. A descriptive analysis will initially be conducted to obtain a general picture of the sample. Time and important covariates (e.g., demographics) as they relate to our outcome variable will be explored. Univariate association tests will be performed to clarify the unconditional effect of these covariates on outcomes.

After the quantitative and qualitative data have been analyzed, summarized, and interpreted independently, the primary focus of the integrated analysis will be on identifying and discussing to what extend and in what ways the qualitative results help to explain the quantitative results (explanatory design). Implementing a “hybrid” approach (104) that will be used for qualitative data.

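### The stated 80% power ignores the small number of CESFAMs: on 14 cluster degrees of freedom it is about 74-75% for users and, unadjusted at the recruitment floor, 76-77% for providers

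*Protocol article*

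**What the plan says.** All of this is in the protocol article, under Specific objective 3, quantitative component.

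- **Providers (OMS-HC).** The starting point is that the "mean ± SD score for the OMS-HC scale was 48 ± 8.3 points". The article assumes "an estimated effect size of 10% in the intervention arm and a placebo effect of 3% in the control arm", giving "43.2 ± 8.3 in the intervention group and 46.6 ± 8.3 in the control group". Under individual randomisation, "with an α = 5% and statistical power of 80%, the minimum sample size per arm is 94 individuals"; this becomes 105 after 10% loss. The ICC is set at 0.05.
- **Clusters.** From 105 and 0.05 the article concludes that "the minimum number of clusters required is equal to: [105*0.05] = 5 clusters". It then says that a larger number of clusters keeps 5% significance and 80% power with fewer people in each: "if 8 clusters per arm is considered (16 CESFAM total), it is necessary to recruit a minimum of 36 professionals per CESFAM".
- **Users (ISMI).** Means of 10.23 and 8.79 with SD 4.74 give 169 per arm. With ICC 0.01 and 8 clusters per arm, "it is necessary to recruit a minimum of 27 PHC users per CESFAM, or 216 users in each arm". The baseline and end-point samples are cross-sectional, not a cohort.
- **Analysis.** The Data analysis section describes mixed-effect models for both groups, with CESFAM as a random effect and study group as a fixed effect.

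**The concern.** When whole CESFAMs are randomised and CESFAM is a random effect, the arm difference is judged against variation between CESFAMs. Sixteen clusters in two arms leave 16 - 2 = 14 degrees of freedom for that variation, or 12 if the three regional randomisation strata are also fitted. The critical value on 14 degrees of freedom is 2.145, against 1.960 for the normal distribution. A cluster size that only just reaches 80% on the normal quantile must fall short on the t reference.

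The consequence lies in interpretation. A null result, above all for users, would be read as coming from a trial with an 80% chance of detecting the assumed effect, when the chance was nearer three in four. The minimum cluster count is a separate slip: a lower bound was rounded down, so a later trial that reused the sentence would start from a wrong figure.

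**Working it through.** **Inputs (all from the article).** Providers: SD 8.3; difference 46.6 - 43.2 = 3.4 from the printed means, or 48 × (0.10 - 0.03) = 3.36 unrounded; loss 10%; ICC 0.05; k = 8 per arm; m = 36. Users: SD 4.74; difference 10.23 - 8.79 = 1.44 printed, or 10.34 × 0.14 = 1.4476 unrounded; ICC 0.01; k = 8; m = 27. Sidedness is not stated; two-sided 5% reproduces the figures.

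**1. Reproducing the article's figures**

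Individual randomisation: n = 2(1.960 + 0.842)² SD²/Δ².

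- Providers: 2 × 7.849 × 68.89/11.56 = 93.5, so 94; 94/0.9 = 104.4, so 105.
- Users, with 1.4476: 168.3, so 169. (The printed 1.44 gives 171.)

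Cluster size: m = n(1 - ICC)/(k - n × ICC).

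- Providers: 105 × 0.95/(8 - 5.25) = 36.27, given as 36.
- Users: 169 × 0.99/(8 - 1.69) = 26.5, so 27.

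The published sizes are therefore the normal-approximation answers.

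**2. Power with 16 clusters**

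Design effect D = 1 + (m - 1) × ICC. Noncentrality λ = Δ / (SD × √(2D/(km))). Power is taken from the normal distribution, and then from the noncentral t on 14 and 12 degrees of freedom. After 10% loss, m = 36 × 0.9 = 32.4 providers.

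| Case | Δ | D | λ | Normal | t, 14 df | t, 12 df |
|---|---|---|---|---|---|---|
| Users, m = 27 | 1.44 | 1.26 | 2.813 | 80.3% | 74.4% | 73.3% |
| Users, m = 27 | 1.4476 | 1.26 | 2.828 | 80.7% | 74.9% | 73.8% |
| Providers, m = 32.4 | 3.4 | 2.57 | 2.909 | 82.9% | 77.2% | 76.1% |
| Providers, m = 32.4 | 3.36 | 2.57 | 2.875 | 82.0% | 76.2% | 75.2% |
| Providers, m = 36, no loss | 3.4 | 2.75 | 2.964 | 84.2% | 78.7% | 77.7% |
| Providers, m = 36, no loss | 3.36 | 2.75 | 2.929 | 83.4% | 77.8% | 76.7% |

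To reach 80% on 14 degrees of freedom with 8 CESFAMs per arm would take 32-33 users per CESFAM, or 45-48 providers recruited per CESFAM with 10% loss.

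**3. Can baseline data recover the loss?**

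*Providers.* They are followed from baseline. If adjustment for baseline OMS-HC multiplies the variance by 1 - r², an assumed r = 0.3 gives 80-81% at 32.4 completers per CESFAM, and r = 0.5 gives 87-88%, both on 14 degrees of freedom. The article states no correlation.

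*Users.* There is in general no individual baseline to adjust for; only a CESFAM baseline mean exists. With 27 users and ICC 0.01, the reliability of that mean is 27 × 0.01/1.26 = 0.214. Even if CESFAM effects were perfectly stable over time, the variance would fall only by 0.214² = 4.6%. λ would then rise to 2.88-2.89, for about 76-77% power.

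**4. Minimum number of clusters**

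105 × 0.05 = 5.25. The formula in step 1 needs k greater than 5.25. At k = 5 it returns 105 × 0.95/(5 - 5.25) = -399, and the effective size per arm cannot exceed 5/0.05 = 100, below 105. At k = 6 it gives m = 105 × 0.95/(6 - 5.25) = 133. The minimum on the article's own inputs is 6 per arm.

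**The case against.** **The provider figure describes a floor and a simple analysis.** The article gives 36 as a minimum, recruits all providers with direct user contact under a census approach, and admits only CESFAMs with at least 50 staff. Providers are measured four times, and the model has individuals as random effects. This stands: 76-77% is the power of an unadjusted end-point comparison at the floor, and actual provider power could reach 80%. It cannot be assumed, because not all staff have user contact or will respond, and no correlation is given. None of it helps the user outcome, where 27 is also a minimum but no census is planned.

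**The normal approximation is a standard planning tool.** True, and the article's arithmetic follows it correctly. The approximation is poor at 8 clusters per arm, however, and costs about 6 points here, while the text asserts 80% without qualification.

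**Five clusters could work.** The 105 already includes attrition. With the 94 evaluable, five clusters reach 80% on a normal test at about 298 completers each. So the stronger reading, that five clusters could never work on any basis, goes too far. Against the article's chosen 105 the count is still rounded the wrong way, and on a t test with 8 degrees of freedom five clusters never exceed about 72%.

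**Type I error.** The Data analysis section names its software as "specifically, using POC MIXED and PROC GENMOD", and a reader might infer an uncorrected GEE test, which with 8 clusters per arm would run at about 8.8%. The article does not support that. It specifies a mixed model with CESFAM as a random effect, assigns GENMOD to no outcome and mentions no sandwich variance. The reference distribution is commonly left to the analysis plan.

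**Conclusion.** The power statement is wrong as written, by a modest amount. For users, the design has 74-75% power on 14 degrees of freedom (73-74% on 12), not 80%, and baseline data offer little to recover it. For providers, the unadjusted end-point comparison at 36 per CESFAM has 76-77% after 10% loss and 78-79% with none; 80% is plausible only with more providers or with baseline adjustment. These figures take the article's own means, SDs and ICCs as given, and assume equal cluster sizes and a two-sided 5% test.

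The minimum of 5 clusters is a rounding error that should read 6. No design choice rests on it, because the trial uses 8 per arm.

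**What to change.** 1. Restate user power as about 75% for 27 users in each of 8 CESFAMs per arm, on 14 cluster degrees of freedom.
2. Restate provider power as about 76-77% at the minimum of 36 per CESFAM after 10% loss. Alternatively, keep 80% but state it as conditional on adjustment for baseline OMS-HC, with the assumed correlation given.
3. Correct the minimum from 5 to 6 clusters per arm.

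The cost is a few lines of text, with no change to enrolment or design.

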CESFAM users will be recruited for participation in baseline and end-point data collection regarding their experiences of stigma by PHC providers. These users must be over the age of 18, have received treatment for MISUI at the CESFAM in the 3 months prior to participation (though not necessarily by a mental health professional), and have a MISUI diagnosis. User MISUI may be diagnosed by a health practitioner or self-diagnosed. Since stigma is a barrier to seeking and receiving help, it is important to include participants who have not been formally diagnosed by a healthcare provider. A research team member will approach users at the waiting room and screen them for inclusion and exclusion criteria. Users in capacity to consent will be invited to sign the consent form and those who sign will be part of the face-to-face survey assisted by a research team member on the same day in the same health facility. To assess capacity to consent, a Spanish adaptation of dimensions and criteria of the Macarthur Competency Assessment Tool for Clinical Research (MACCAT-CR) (95) are used. This process includes the following actions; (1) The interviewer exposes the user to the relevant information of the project after which he/she is questioned about what has been explained (comprehension); (2) Subsequently, they are asked about their appreciation or assessment of the information provided in their specific circumstances; and (3) A reasoned reflection on the decision to be made is promoted, assessing the circumstances and consequences, to end up expressing their choice.

The primary outcome for users will be measured using The Internalized Stigma of Mental Illness (ISMI) scale, validated for the Chilean population (96). The study will collect cross-sectional samples at baseline and end-point data collection and compare average scores between intervention and control groups for baseline and end-point measures.

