A face-to-face survey assisted by a research team member will be used to examine how users perceive stigmatizing attitudes and behaviors among CESFAM PHC (97) providers. The questionnaire will include four main components: (1) socio-demographic and other relevant general variables; (2) perceived stigmatizing attitudes and behaviors among CESFAM PHC providers; (3) perceived recovery-oriented practices by CESFAM PHC providers; and (4) accessing healthcare at their CESFAM. Subjective experience of stigma as conveyed by CESFAM PHC providers will be measured among patients using validated tools. The Perceived Devaluation-Discrimination Scale will be used to assess the extent to which users believe that other people devalue or discriminate against someone with MISUI. This scale has shown acceptable internal consistency (*a* = 0.78) (97). The tool is validated in Chile (98). An adapted version of the Discrimination Experience Subscale of the 29-item ISMI scale was designed to measure the subjective experience of stigma, e.g., respondents’ perceptions of how they are treated by others. It measures alienation, stereotype endorsement, perceived discrimination, social withdrawal, and stigma resistance. The Cronbach’s alpha value of the total score was 0.83 and the Spearman-Brown Coefficient of 0.76 (99). For FONDECYT N° 1160099 (34), a shortened version of the ISMI scale was used, which was validated for use in Chile with an (*a* = 0.916) (96). The Person in Recovery Version of the RSA will also be considered to assess users’ perceptions of recovery-oriented practices in their CESFAMs. Due to the sensitive nature of the study scales, there is some risk of social desirability bias in participants’ responses. Both PHC providers and users will complete the Marlowe-Crowne Social Desirability Scale (MCSDS). The MCSDS will allow to measure and control such bias. The scale has 33 items which were defined to be culturally acceptable but unlikely to occur, and to have minimal abnormal implications for either the socially desirable or socially undesirable responses (100).

1. b Qualitative component:

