**FIGURE 5 F5:**
[figure not shown]
Study activities.

This intervention is expected to promote the following outcomes; Participation in the experimental group will result in a significant decrease in stigmatizing attitudes among PHC providers toward individuals with MISUI compared with the control group as measured by the Chilean version of the OMS-HC; Participation in the experimental group will result in a significant decrease of PHC users experiences of stigma conveyed by PHC providers compared with the control group as measured by the ISMI scale, validated for the Chilean population; The changes in attitudes and behaviors within the experimental group will be sustained over time as measured at 6 months-follow-up.

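### The user hypothesis claims less stigma conveyed by PHC providers, but the primary scale, the ISMI, is not shown to measure stigma from providers, and its version is not clearly fixed

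*Protocol article*

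**What the plan says.** All of this is in the protocol article.

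- **Primary outcome for users** (Specific objective 3, quantitative component): "The primary outcome for users will be measured using The Internalized Stigma of Mental Illness (ISMI) scale, validated for the Chilean population", citing reference 96. Separate cross-sectional samples at baseline and end-point are compared between arms.
- **Hypothesis** (Abstract, Methods; repeated after Figure 5): participation should bring a "significant decrease of PHC users experiences of stigma conveyed by PHC providers" relative to control, with the ISMI as the measure.
- **Instrument description** (Specific objective 3, user survey paragraph): "An adapted version of the Discrimination Experience Subscale of the 29-item ISMI scale was designed to measure the subjective experience of stigma", explained as "respondents’ perceptions of how they are treated by others". The next sentence reads "It measures alienation, stereotype endorsement, perceived discrimination, social withdrawal, and stigma resistance". A total-score alpha of 0.83 follows (reference 99). For the earlier Chilean study, the text says "a shortened version of the ISMI scale was used, which was validated for use in Chile", with alpha 0.916 (reference 96).
- **Sample size** (same section): "the mean ± SD for the ISMI score was 10.34 ± 4.74 points", taken from that earlier study.
- **Components that reach users** (Specific objective 2): the awareness media are aimed at providers and users, and the arts programme enrols ten users per CESFAM for 10 weeks.

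**The concern.** There are two linked problems.

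The first is the match between claim and measure. Internalized stigma is what a person has taken on about themselves. Stigma conveyed by providers is what staff do or express. A score made up mainly of the former can move without the latter, and the reverse is also true. If the report follows the stated hypothesis, a fall in ISMI would be presented as a change in provider behaviour as felt by users. Equally, a null ISMI result could be read as no change in provider behaviour when the scale may have been a poor detector of it.

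The second is which ISMI is scored. The paragraph that should settle this describes an adapted subscale and a shortened scale, and gives the subscale more content than its name allows. The planning mean and SD can belong to only one of them.

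**Working it through.** **1. The plan's own figure.** Inputs from the user sample-size paragraph: mean 10.34, SD 4.74, falls of 1% (control) and 15% (intervention), α = 5% (two-sided assumed; the text does not say), power 80%, ICC 0.01, 8 clusters per arm.

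- Difference: 10.34 × (0.99 − 0.85) = 1.4476.
- Individual randomization: n = 2 × (1.96 + 0.8416)² × 4.74² / 1.4476² = 168.3, so 169 per arm, as stated. The rounded means (10.23 − 8.79 = 1.44) give 171, and 1.45 gives 168.
- Users per cluster: m = n(1 − ICC) / (k − n × ICC) = 169 × 0.99 / (8 − 1.69) = 26.5, so 27 per CESFAM, 216 per arm and 432 in total, as stated.
- Back-check: design effect 1 + 26 × 0.01 = 1.26; effective size 216 / 1.26 = 171.4 per arm; power 80.3% for a difference of 1.44 (normal approximation).

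The arithmetic is sound for whichever score has mean 10.34 and SD 4.74.

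**2. Which score that is.** The figures come from the earlier study, and the article says that study used the shortened ISMI (reference 96). The primary-outcome sentence also cites reference 96. Primary outcome, planning figures and shortened version therefore form one plausible chain, although no sentence states it. The adapted subscale stands outside the chain: its alpha is 0.83 rather than 0.916, its source is reference 99, and no mean or SD is given for it.

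**3. The internal contradiction.** The adapted instrument is called one subscale, about experience of discrimination. The following sentence gives it five domains and a total score. Both cannot describe the same instrument.

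**4. Claim against content.** The five listed domains, compared with stigma conveyed by providers:

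| Domain | About how the user is treated? | Limited to providers in the text? |
|---|---|---|
| Alienation | No | No |
| Stereotype endorsement | No | No |
| Perceived discrimination | Yes | No (others in general) |
| Social withdrawal | No | No |
| Stigma resistance | No | No |

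At most one of five concerns treatment, and its stated referent is others in general.

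**5. Other routes to a lower score.** Awareness media run through months 1–18 for providers and users. The arts programme takes ten users per CESFAM, so 8 × 10 = 80 users across the intervention arm, and ends in an exhibition. Either could lower internalized stigma with no change in provider conduct. The documents do not allow the size of this route to be estimated. End-point users are a fresh waiting-room sample, so few may have attended the workshops.

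**The case against.** The best defence is that the plan is coherent if read generously. Only one sentence designates a user primary outcome, and it shares its citation with the shortened Chilean version. The subscale sentence is in the past tense and may be background. The five domains may belong to the 29-item scale just mentioned, which would make the problem a misplaced pronoun. The survey paragraph frames the questionnaire around provider attitudes and behaviours and says that stigma from CESFAM providers will be measured with validated tools. The item wording may name providers, and an article can leave that wording to the full protocol.

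Much of this stands. It rules out several stronger readings that a reader might infer:

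- *Three different ISMI instruments.* The shared reference 96 makes the designated primary and the shortened version most likely the same scale, so at most two versions compete.
- *The outcome is definitely an internalized-stigma score.* If the adapted discrimination subscale were scored, the construct would be closer to the hypothesis. The planning figures would then lose their source, and the referent would still be others in general.
- *A positive result would support nothing.* Randomization would still support an intervention effect on users' ISMI score. What is in doubt is attributing it to providers.
- *The trial is underpowered because of this.* No mean, SD or effect is given for the adapted subscale, so its power cannot be computed, and any assumed shrinkage of the effect would have no source here.

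What the defence does not remove is the gap between claim and description. The article chooses to describe the instrument. That description contradicts itself and does not tie the items to CESFAM staff, while the hypothesis does.

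**Conclusion.** The concern holds in a limited form. As written, a fall in ISMI relative to control could be reported as an effect on users' ISMI score, but not as less stigma conveyed by PHC providers. The description also leaves two ISMI versions in play and credits a single subscale with five domains.

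In extent, it touches the interpretation of the whole user comparison. It does not touch the stated sample size, which reproduces, and no loss of power is established. The provider primary outcome (OMS-HC) is unaffected.

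The conclusion rests on the article's own description of the scale. If the items actually scored name CESFAM providers, the mismatch of construct largely disappears and only the description needs correcting. The documents do not show those items.

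**What to change.** 1. In the primary-outcome sentence and the user survey paragraph of Specific objective 3, state that the user primary is the ISMI version and score that produced 10.34 ± 4.74. On the article's account this is the shortened Chilean version; confirm it against the earlier study.
2. In the user survey paragraph, correct the sentence that credits the Discrimination Experience Subscale with five domains. Say whether the adapted subscale is used in this trial at all and, if so, in what role.
3. In the Abstract and the expected-outcomes text after Figure 5, reword the user hypothesis, and any conclusion drawn from it, to the construct that the named score measures. Keep the attribution to PHC providers only if the scored items name CESFAM providers, and say so.

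The cost is wording in these places and, unless the items do name providers, a narrower headline claim for users. The sample size needs no change if the score in step 1 is confirmed.
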